## Abstract

**Introduction:**

Hearing and vision impairments are prevalent among residents in long‐term care settings. Hearing and vision impairments frequently go unsupported, affecting residents' quality of life and healthcare costs. This paper describes the protocol for a pre−post evaluation and process evaluation of a pragmatic sensory support intervention (SSI) that was developed with residents, informal caregivers and long‐term care workers.

**Methods and Analysis:**

A prospective pre−post‐intervention trial within long‐term care will be conducted, including three groups: residents (*n* = 87), informal caregivers (*n* = 87) and long‐term care workers (*n* = 40). Outcome measures include health‐related quality of life and well‐being measures relevant to each group measured at baseline, 3‐ and 6‐months post‐intervention. Health resource and sensory device utilisation will be captured from routine data and by direct observation. Qualitative interviews, including a representative sample of residents and informal caregivers, will be conducted as part of a simultaneous process evaluation. Generalised linear models and paired *t*‐tests will be used to evaluate the effects on residents' and caregivers' quality of life and sensory device use. The cost‐effectiveness of the intervention will be examined using within‐trial analysis, economic modelling and budget impact assessment. A process evaluation will use descriptive statistics and thematic analysis to assess the intervention's reach, adoption, implementation, acceptability, mechanisms of change and contextual influences.

**Conclusion:**

Hearing and vision impairments are common but under‐supported in older adults in long‐term care. This protocol involves a systematic evaluation of the effectiveness and implementation challenges of a pragmatic SSI to optimise hearing and vision function and improve the quality of life for long‐term care residents and their caregivers.

## Introduction

1

Hearing impairment, vision impairment and dual sensory (i.e., both hearing and vision) impairment are highly prevalent among people resident within long‐term care settings [2, 3, 4, 5]. Among 4007 residents living in long‐term care across eight European countries, 32% had a dual sensory impairment, 12.3% had hearing impairment only (based on the InterRAI instrument for long‐term care facilities) [6] (REF), with hearing impairment defined as difficulty hearing (e.g., when a person speaks softly and is more than 6 feet away) to no hearing aid all, even with the use of hearing aids), and 19.5% had vision impairment (difficulty seeing [e.g., large print] to having no vision at all, even with the use of glasses or other visual aids) [2].

Approximately half of the residents wore glasses or used another visual appliance and 9% used hearing aids [2]. Sensory impairments exacerbate the impact of cognitive impairment or dementia, and for those living with dementia, management of hearing and vision impairment is more complex [7, 8, 9, 10]. Hearing and vision impairment both result in communication difficulties and difficulties reading text or understanding visual information. These functional difficulties can be masked by dementia or mistakenly attributed to cognitive impairment rather than recognised as a potentially treatable sensory impairment [9, 11].

It is important that sensory impairments are effectively managed in long‐term care settings as both result in activity limitations and participation restrictions, which may negatively impact overall well‐being. Both hearing and vision impairment separately are associated with loneliness [12, 13, 14, 15], anxiety [16, 17] and depression [17], with even worse outcomes for those with dual sensory impairment [17, 18].

Unfortunately, sensory impairments are underdiagnosed and poorly managed in long‐term care settings [19, 20, 21]. Reasons for poor management include a lack of knowledge among long‐term care staff regarding amplification devices [21], how to care and manage devices [22, 23], and an overall lack of training to use hearing and vision devices [22, 23, 24]; sensory needs not prioritised among staff [24, 25]; unclear referral pathways and difficulties accessing hearing and vision services [22, 26, 27, 28]; and a lack of suitable hearing and vision screening tools/protocols for people with dementia [29].

To address these challenges and support long‐term care staff to deliver high‐quality hearing and vision support to residents, we drew on behavioural science frameworks and principles [30, 31] to identify key needs and corresponding components of a sensory support intervention (SSI) and to understand barriers to implementation so that these could be addressed [32, 33]. The intervention aims to support long‐term care staff in (1) assisting residents with day‐to‐day device management and (2) communicating effectively with residents who have hearing and/or vision impairment [32, 33, 34]. Delivery of the intervention is supported by sensory champions identified from among long‐term care staff who will be responsible for identifying residents' hearing, vision and communication needs and preferences, increasing awareness of hearing and vision services available and carrying out an audit of residents' rooms and living areas to optimise them for sensory functioning (e.g., reducing background noise). Champions have proved to be effective in supporting long‐term care workers in relation to quality of care and improved resident health outcomes [35], including maintaining hearing aids and using communication strategies for residents with hearing impairment [36].

## Research Questions

2

This study uses prospective pre−post‐intervention trial design. The primary research question (RQ) is:

What is the impact of the SSI on the quality of life of residents and their informal caregivers (i.e., unpaid care provided by family, close relatives and friends) [37]? This RQ will be explored through standardised questionnaires (e.g., the Health Utilities Index 3 [HUI‐3] [38] and the Quality of Life‐Aged Care Consumers questionnaire [QOL‐ACC] [39], described below).

Secondary research questions include:

What is the impact of the SSI on care workers' (formal caregivers of people living in long‐term care) use of sensory support behaviours? This RQ will be explored through direct observation and questionnaires.

What is the impact of the SSI on residents' use of hearing and vision devices, quality of resident‐staff communication, well‐being, sensory function and behaviour? This RQ will be explored through direct observation, self (or proxy) report questionnaires and professional caregiver report.

What is the impact of the SSI on informal caregivers' well‐being and relationship with residents? This RQ will be explored through questionnaires.

What is the cost‐effectiveness of the SSI compared to standard care? This RQ will be explored through direct observation and questionnaires.

A simultaneous process evaluation is also planned to address the following research questions:

To what extent was the SSI considered acceptable to care workers, residents and informal caregivers and implemented as intended? Acceptability will be explored through a post‐intervention survey and individual structured qualitative interviews, and implementation will be evaluated based on inspection of daily task sheets that record the daily duties of care workers.

What were the mechanisms through which the SSI achieved/did not achieve impact? This RQ will be explored using individual, semi‐structured, in‐depth interviews.

How did contextual factors impact the implementation of the SSI? This RQ will be explored by analysing the written log completed by the sensory champion, supplemented by a structured qualitative interview.

## Methods and Analysis

3

### Sample

3.1

Participants will include three groups: (1) people living in long‐term care, (2) informal caregivers of people living in long‐term care and (3) long‐term care workers. All participants will be recruited from a single long‐term care setting in Perth, Western Australia, who we partnered with to develop the intervention. All people living at the participating long‐term care setting over the age of 65 will be eligible to take part, irrespective of their sensory or cognitive functioning. Informal caregivers will be eligible to participate if they are aged 18 years or older and are a family member or friend of a resident participating in this study. Informal caregivers will be excluded if they are not in regular contact with the resident. Long‐term care workers will be eligible to participate if they currently work in the participating long‐term care setting and are involved in the provision of daily personal care to residents participating in this study.

### SSI

3.2

The SSI is twofold. First, we will be intervening directly with long‐term care workers to support them to carry out three target behaviours: (1) assist residents with day‐to‐day hearing and vision device use, (2) use appropriate communication and (3) mute TV/radio at the bedside and during mealtimes when communicating. These behaviours are fully specified in Table 1. We will be carrying out a multifaceted intervention that addresses the key barriers and enablers identified in our exploratory Phase 1 research [32, 33, 34], as described in Table 2. Second, one or two staff at each participating site will be assigned a ‘sensory champion role’. Previous studies have shown that designating one or more staff members as ‘champions’ in long‐term care facilities and providing them with additional training and responsibilities can enhance their competence in managing related issues, improve the quality of care and positively impact the health outcomes of residents [35]. A subsequent study reported that designated ‘hearing champions’ were effective in supporting staff in relation to the maintenance of hearing aids and the use of communication strategies for residents with hearing impairment [36]. The sensory champion may be a registered nurse, care worker or therapy assistant, and will be employed in this capacity for 2−3 days per week for 3 months at each site. A description of the tasks completed by the sensory champion is outlined in Table 3.

**Table 1 hex70175-tbl-0001:** Full specification of staff behaviours targeted in the sensory support intervention.

Behaviour	Full specification
Assist residents with day‐to‐day hearing/vision device use	Each morning, check glasses are on and clean (glasses wearers) Each morning, check that hearing aids are on, inserted correctly and on correct ears and working (HA users) Each evening, check hearing aids and personal listening devices are removed, wiped clean and stored safely and batteries are conserved (on charge/battery door open) (HA/ALD users) Each week, check frames are well aligned and in good order (e.g., screws tight, nose pads intact, no corrosion of metal frames or fragmentation of plastic) (glasses wearers)
Use appropriate communication	Gain attention Speak face‐to‐face Speak clearer, nearer, slower Make text brighter, bigger, bolder
Make small changes to residents' environment	Request permission to mute TV or radio before talking to residents in their room Turn off music/TV in communal areas during mealtimes

Abbreviations: ALD = assistive listening device, HA = hearing aid.

**Table 2 hex70175-tbl-0002:** Summary of sensory support intervention for long‐term care workers.

Intervention component	Barrier that is being addressed	Description
Mastering sensory support Education and training, delivered by lead sensory therapist Training materials were developed by experts in audiology and optometry, supplemented by resources from our international collaborators and leading organisations such as Hearing Australia.	Knowledge and skills related to: Device management: This includes understanding different types of sensory devices, caring for these devices, inserting and removing hearing aids and ensuring they are working properly.	Tailored to each centre, a 60 min education and training session will be held on multiple days, either before or shifts. Training will be delivered by a member of staff at each centre. These sessions will cover the following topics: Device management. Effective communication with residents who have sensory impairment and/or dementia. Support good sensory cognitive health: support device use, reduce background noise and support the behaviour of residents with dementia while fostering an environment that respects their choices and preferences.
	Interpersonal skills: The ability to respond effectively to residents' negative reactions and behaviours, particularly those exhibited by residents with dementia. Background noise impact: Knowledge of how background noise affects residents with sensory impairment.	
Sensory support goal setting	Long‐term care staff are task‐orientated.	Task list: Integrating sensory support items (support device use, effective communication and reduction of background noise) into the staff's daily task list. Staff recognition: ‘Sensory support star’.
Sensory support station	Devices are not always accessible as they are easily lost. Devices are not labelled.	Designate specific areas within residents' rooms and communal areas as dedicated sensory stations equipped with sensory devices (e.g., hearing aids, glasses), cleaning and maintenance kit. Labelling options will be discussed with residents.
Sensory support prompt Use of visual cues and reminders in strategic locations	Forgetfulness to enact sensory support behaviours.	Tailored to each centre, use a physical prompt (e.g., a poster placed on the back of the main door of the resident's room).

**Table 3 hex70175-tbl-0003:** Summary of sensory champion role.

Intervention component	Description	Duration
Understand hearing and vision function	Baseline data pertaining to hearing and vision function collected by the research team will be shared with the sensory champion. NB: if the intervention is shown to be effective, we will advocate for screening measures to be incorporated into routine care.	NA (incorporated into data collection)
Sensory needs analysis	The sensory champion will extract hearing and vision records from the resident's chart (if available), confirm they are up‐to‐date, and discuss their preferences regarding hearing and vision device use and communication strategies.	Approximately 60 min
Provide information about intervention pathways	Based on the sensory needs analysis, residents will be provided with information about potential intervention pathways (if required).	Approximately 30 min
Sensory support station and sensory support prompt discussion	Discussions with residents about their preference for a designated area to store and maintain all their sensory support devices and related items. Additionally, discuss whether they are agreeable to placing visual prompts to remind staff of sensory support‐related tasks.	Approximately 30 min
Environmental audit	Residents' rooms will be audited to ensure they are optimally set up for hearing and vision impairment.	Approximately 30 min
Device troubleshooting and repair	Aged care staff will be informed that they can contact the Sensory Champion should a resident's hearing/vision aids stop working. The Sensory Champion will try to troubleshoot the problem (based on their training) and arrange for repair if required.	As needed
Referral to hearing and vision specialists and GPs	If requested, the Sensory Champion will facilitate referral to appropriate hearing, vision or medical services (e.g., for ear wax management and supported administration of eye drops).	As needed

All residents with dementia will be encouraged to have a family member accompany them to assessment appointments and appointments with a sensory champion. For residents with dementia who may revert to their first language, we will seek input from family members, who may be able to translate, use gestures to communicate or utilise translation apps. We will also consult with long‐term staff who care for the resident to identify communication preferences.

### Sample Size Calculation

3.3

Approximately 87 residents will be recruited at baseline. The evaluation is powered to detect a standardised effect size of *d* = 0.3 (because hearing/vision interventions are associated with small‐to‐medium effects on health‐related quality of life outcomes in the primary treatment group (i.e., residents) [40, 41, 42]. Assuming a correlation of 0.6 between baseline and 12‐week follow‐up Health Utility Index‐3 (HUI‐3) scores and an attrition rate of 20% at follow‐up (a conservative estimate based on the 12%–15% rates observed in previous similar studies) we will need to recruit 87 residents at baseline to achieve 80% power to detect the effect size at the two‐sided 5% level of significance, according to estimates generated by G*Power software [43].

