### Outcome Measures

3.5

To evaluate intervention effectiveness, participants will undergo assessment at baseline, throughout the intervention, and at 3 and 6 months post‐intervention. Data will be derived from a variety of methods, including self‐ or proxy‐report questionnaires; long‐term care records; participant observation and qualitative interviews.

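### Under the stated inputs and 20% attrition, 80% power needs 90 residents; the stated 87 gives about 78% to 79% (a minor correction)

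*Protocol article*

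**What the plan says.** All the inputs are in the Sample Size Calculation section of the protocol article (3.3):

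- Effect: "The evaluation is powered to detect a standardised effect size of" 0.3, in residents.
- Correlation: "Assuming a correlation of 0.6 between baseline and 12‐week follow‐up Health Utility Index‐3 (HUI‐3) scores".
- Loss: "an attrition rate of 20% at follow‐up", which the section describes as "a conservative estimate based on the 12%–15% rates observed in previous similar studies".
- Test level: "at the two‐sided 5% level of significance".
- Result: "we will need to recruit 87 residents at baseline to achieve 80% power to detect the effect size". The section names G*Power as the source and introduces 87 as an approximate number.

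The section does not give the number of completers needed, name the test, or say how attrition was applied. The design is a single-group pre-post comparison, so a paired comparison of baseline with follow-up is the natural reading of an effect size combined with a correlation.

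**The concern.** A number of completers is turned into a recruitment target by dividing by one minus the attrition rate. Multiplying by one plus the rate is a common slip and always gives too few. Here the paired calculation followed by that multiplication lands exactly on 87, while the division lands on 90. If 87 is too low for 20% attrition, the power sentence does not follow from its own inputs. Part of the safety margin implied by calling 20% conservative would then be missing as well. The figure matters because 87 is the headline resident sample in the abstract, and because the Discussion defends the small sample as sufficient, with this section as its only quantitative support.

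**Working it through.** **Inputs (Sample Size Calculation):** d = 0.3, correlation r = 0.6, two-sided alpha 0.05, power 0.80, attrition 20%, recruitment target 87. Assumption: d is standardised by the SD of a single measurement, with equal SDs at both times. This is the reading under which the correlation enters the calculation.

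**1. Effect on the paired scale.** dz = d / sqrt(2(1 - r)) = 0.3 / sqrt(0.8) = 0.3354.

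**2. Completers needed.** Power of the paired t test from the noncentral t distribution with n - 1 degrees of freedom and noncentrality dz x sqrt(n), the method G*Power uses for paired means:

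| Completers | Power |
|---|---|
| 69 | 78.4% |
| 70 | 79.0% |
| 71 | 79.6% |
| 72 | 80.2% |

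The smallest number that reaches 80% is 72. A repeated-measures F test with two measurements and f = 0.15 also gives 72.

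**3. Reproducing 87.** Two routes come close:

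- 72 x 1.2 = 86.4, rounded up to 87. This is an exact match, but with the wrong inflation.
- Normal approximation: ((1.960 + 0.8416) / 0.3354)^2 = 69.77 completers; 69.77 / 0.8 = 87.2, or 70 / 0.8 = 87.5. The inflation is correct. Rounding up gives 88, so 87 requires rounding down.

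Other readings do not give 87 under the stated two-sided test. Taking dz = 0.3 directly needs 90 completers (113 recruited). A reduction of the ANCOVA type needs 58 (73 recruited).

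**4. Correct inflation.** 72 / (1 - 0.20) = 90 residents, which is 90 - 87 = 3 more than stated.

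**5. What 87 delivers at 20% attrition.** 87 x 0.8 = 69.6, so 69 to 70 completers and 78.4% to 79.0% power. The shortfall is 80 - 79.0 = 1.0 to 80 - 78.4 = 1.6 points. The effect detectable with 80% power is d = 0.304 with 70 completers and 0.306 with 69.

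**6. Attrition that 87 can absorb.** 1 - 72/87 = 17.2%. At the cited rates, 87 x 0.85 = 73.95 and 87 x 0.88 = 76.56. About 73 to 77 residents would therefore remain, with power of about 81% to 83%.

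**The case against.** The strongest reply is that the discrepancy is too small to matter. The target is given as approximate, the gap is 3 residents, and the detectable effect moves only from 0.300 to about 0.305. The 20% is itself set above the attrition seen in earlier studies; at those rates 87 gives more than 80% power. All of this stands, and it limits the point to a minor one. It does not make the sentence correct, because the protocol chose 20% as its planning value and claims 80% power at that value.

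The second reply is that the cause is unknown. A reader might infer that the authors certainly multiplied by 1.2. The documents do not support that: neither 72 nor a factor of 1.2 is printed, and a normal approximation with the correct division gives 87.2. The multiplication fits better, since it gives 87 exactly with the usual rounding up and with the method of the named software, but it remains an inference. The shortfall under the t test does not depend on which route was taken.

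**Conclusion.** The point holds in a limited form. Under the stated inputs and the exact paired t method, 80% power with 20% attrition needs 90 residents, and 87 gives 78.4% to 79.0%. The result rests on reading d as standardised by the single-measurement SD and on a t-based calculation. By the normal approximation, 69 to 70 completers would give 79.6% to 80.1%, which is essentially the stated power. Severity is minor: a stated figure is slightly off, and the trial is not materially underpowered for this reason.

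A reader might go further and infer much lower power at later visits, because the calculation refers to a 12-week follow-up while outcomes are also taken later. The documents do not support a figure for that. They give no attrition rate per period, so compounding 20% over successive 12-week spells has no basis, and they do not fix whether the 3- and 6-month visits are counted from baseline or from the end of the intervention. Powering one time point while measuring others is also ordinary practice. No conclusion about the later visits is drawn here.

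**What to change.** Amend the Sample Size Calculation section in one of two ways:

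- Keep 87 and restate the power as about 79% at 20% attrition, or equivalently as 80% with attrition up to about 17%.
- Give 90 as the number to recruit for 80% power at 20% attrition.

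In either case, state that 72 completers are needed, name the test, and give the inflation formula: recruits = completers / (1 - attrition). The first option costs only a change of wording. The second costs 3 more residents and a matching change to the resident number in the abstract.

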### Baseline Measurement

3.4

#### Demographics and Health Status

3.4.1

Information pertaining to residents' age, sex, ethnicity, time in long‐term care and level of care need will be extracted from their long‐term care records. Formal and informal caregivers will be asked to complete a purposefully developed questionnaire to document their age, sex, ethnicity and educational level.

